### Randomization

Using a 1:1 allocation, participants will be randomized into either the intervention group or the control group using the “split randomly” function within the TextIt platform [30]. This function randomly passes contacts through approximately equally distributed pathways in the flow and will allocate them to receive either the intervention or the control condition. Randomization will occur after a participant has given birth. Participants will be stratified into 2 groups based on parity (primiparous and multiparous) prior to randomization.

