### Data Analysis

Data will be analyzed on an intention-to-treat basis (excluding women who requested to stop receiving the messages or were lost to follow-up). Demographic characteristics on maternal age, marital status, education level, and delivery method will be expressed as means and standard deviations or percentages, as applicable, based on group allocation. Postnatal contacts for themselves and their infants, health concerns, and feeding behavior will also be expressed as means and standard deviations or percentages, as applicable, based on group allocation. Any significant differences in baseline characteristics, examined through a chi-square analysis or Mann-Whitney test, will be adjusted for in the analysis. A *P* value of 0.05 will be considered significant for all outcomes.

For the primary outcome of self-efficacy, a total score will be reported using means, standard deviations, and percentages. Analysis of covariance (ANCOVA) will be used to measure whether total self-efficacy scores differ between the 2 groups, with adjustments for the pretest scores and any significant baseline characteristics.

For the first secondary objective, an ANCOVA will be used to determine whether scores differ between the 2 groups on social support, postpartum anxiety, and postpartum depression, with adjustments for the pretest scores and any significant baseline characteristics. For the second secondary objective, a 2-way ANCOVA will be used to measure whether the mean difference of self-efficacy scores differs between the 4 groups (multiparous/primiparous and intervention/control), with adjustments for any significant covariates on self-efficacy, social support, postpartum anxiety, and postpartum depression. For the third secondary objective, a 2-way repeated-measures ANCOVA will be used to explore whether changes in the key psychosocial outcome variables varied over time.

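### Covariates for the primary ANCOVA are chosen by baseline significance tests, and parity, the stratification factor, is not in the model

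*Protocol article*

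**What the plan says.** Under Data Analysis, the protocol article gives a rule for choosing covariates: "Any significant differences in baseline characteristics, examined through a chi-square analysis or Mann-Whitney test, will be adjusted for in the analysis". The primary analysis follows it. Its model is set out thus: "Analysis of covariance (ANCOVA) will be used to measure whether total self-efficacy scores differ between the 2 groups". The covariates of that model are then given only in general terms: "with adjustments for the pretest scores and any significant baseline characteristics". The same adjustment is given for the ANCOVAs of social support, anxiety and depression under the first secondary objective.

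Four characteristics are named for description by arm: "Demographic characteristics on maternal age, marital status, education level, and delivery method will be expressed as means and standard deviations or percentages". The list of characteristics to be tested is not closed. The significance level is given for outcomes ("A *P* value of 0.05 will be considered significant for all outcomes"), with no separate level for the baseline tests.

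Under Randomization: "Participants will be stratified into 2 groups based on parity (primiparous and multiparous) prior to randomization". Parity is obtained at screening, before allocation. In the analysis it appears only as a factor for one secondary objective: "For the second secondary objective, a 2-way ANCOVA will be used to measure whether the mean difference of self-efficacy scores differs between the 4 groups".

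**The concern.** Whether two randomised arms differ significantly on a variable is a separate question from whether that variable predicts KPCS score at 6 weeks. A rule based on the first can admit variables that explain nothing and leave out variables that explain a good deal. The content of the primary model is then unknown until baseline data by arm have been examined.

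Parity is the clearest case. The trial randomises within parity groups and sizes itself at the level of parity. Yet parity reaches the primary model only if it happens to be significantly imbalanced, which stratification is meant to make unlikely. At stake are a primary analysis fixed in advance and some precision from information already held for every woman.

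**Working it through.** **The plan's own figure.** The Sample Size section gives 30 per parity-by-arm group, 60 per arm and 140 in total. With a difference of 3.78, SD 4.5, two-sided 0.05 and 90% power (the article states no power, so 90% is an assumption), n = 2 × (1.96 + 1.28)² × (4.5/3.78)², which rounds up to 30. Then 4 × 30 = 120, and 60 × 1.15 = 69, rounded to 70 per arm. This figure is not in dispute. It only supplies the N of 120 used below.

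**Chance that the rule changes the model.** With k independent baseline tests at level 0.05 (assumed) and no true imbalance, P(at least one enters) = 1 − 0.95^k.
- k = 4 (the characteristics named): 1 − 0.8145 = 18.5%
- k = 5: 22.6%
- k = 8: 33.7%
- k = 10: 1 − 0.5987 = 40.1%

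Under a fixed covariate list this probability is zero.

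**When parity could enter.** At 70 per arm, with half the women primiparous (assumption), the standard error of the difference in share primiparous is √(0.25 × 2/70) = 0.085. Parity would reach P<0.05 only at a difference of about 1.96 × 0.085 = 0.166, or 17 percentage points.

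**Size of the effect on the primary test.** A simulation was run with these assumptions, none of which the article supplies: N = 120 with equal parity groups, pretest correlation 0.5, SD 4.5, four further covariates with effects of 0.3, 0.3, 0.2 and 0 SD, and a parity effect of 0.5 or 1.0 SD. There were 6,000 runs per scenario. Power is for a true difference of 2.5 points. Normal-theory tests stood in for the chi-square and Mann-Whitney tests. Each cell gives the results for parity effects of 0.5 / 1.0 SD.

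| Model | Type I, balanced within parity | Type I, unrestricted split | Power, balanced | Power, unrestricted |
|---|---|---|---|---|
| Planned rule | 4.5% / 3.5% | 4.8% / 4.2% | 86.7% / 85.7% | 85.0% / 85.3% |
| Pretest only | 5.1% / 4.0% | 5.6% / 4.7% | 85.7% / 84.9% | 84.5% / 84.6% |
| Pretest + parity | 5.2% / 4.5% | 5.5% / 4.7% | 86.2% / 86.4% | 84.9% / 86.2% |
| Pretest + parity + four covariates | 5.5% / 5.1% | 5.3% / 5.0% | 92.8% / 92.7% | 92.0% / 92.3% |

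The rule selected parity in 0% of runs when allocation was balanced within parity, and in about 5% when it was not. Adding parity to the pretest-only model gained about 0.5 to 1.5 points of power. Against the planned rule itself, pretest plus parity ran from about 0.5 points lower to 0.9 higher, so parity alone is close to neutral. The larger gain, to 92–93%, comes from naming all the prognostic covariates in advance.

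**The case against.** The strongest defence is that the harm is small. The rule looks at baseline data, not outcomes. The pretest score, probably the best single predictor, is always in the model. Parity is modelled under the second secondary objective. The simulation shows no inflation of type I error. All of this stands, and it limits the weight of the point.

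It can also be said that baseline differences here need not be pure chance. Under Screening and Baseline, women learn their allocation before consent and the baseline survey, so differential completion or response is possible and adjustment has a rationale. That is fair, but a significance test cannot separate such differences from chance. It argues for covariates named in advance, and parity, recorded before allocation, is free of the problem.

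A third defence is that an article leaves such detail to an analysis plan. Here, however, the article states the selection rule outright.

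A reader might infer more than the documents support:
- *That the standard error of the primary estimate is wrong because it ignores stratification, and that parity is also left badly imbalanced.* These need opposite allocation mechanisms. If the split is unrestricted within parity groups, the standard error without parity is valid. If it is balanced, the imbalance does not arise. The article says only "This function randomly passes contacts through approximately equally distributed pathways in the flow".
- *That a definite number of KPCS points of imbalance goes unadjusted.* The article's SD of 4.5 accompanies a baseline-to-6-week difference and is not given as the SD of KPCS scores. Pretest adjustment would also absorb part of any parity effect.
- *That the trial expects parity to predict confidence.* No section says so. The hypothesis on parity is one of no difference, most naturally read as being about effect modification.
- *That the lead researcher, who knows allocations, steers the choice.* The Blinding section gives this person the task of summarising data and says nothing of choosing covariates.
- *That the allocation method should be changed.* Blocking detail is commonly left to a full protocol, and recruitment is already under way.

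**Conclusion.** The point holds as one of prespecification and efficiency. The primary and first secondary ANCOVAs rest on a selection rule that does not measure prognostic value, and parity, by which the trial randomises, is not named in them. The chance that the rule adds at least one covariate by chance is 18.5% with four tests and 40.1% with ten, assuming independence and a 0.05 level for the baseline tests. Under the simulation's assumed effects, the planned test is mildly conservative (3.5% to 4.8%) and has 85% to 87% power, against 92% to 93% with a prespecified set that includes the truly prognostic variables. That contrast is a favourable case, because it supposes those variables are correctly named. The benefit from parity alone is modest and depends on an effect on the KPCS that the article does not give. The change should be made, but the validity of the primary test is not threatened.

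**What to change.** Replace the selection rule, and the matching phrases in the primary and first secondary analyses, with: 'The ANCOVA for each outcome includes arm, the baseline value of that outcome, parity, and any prognostic covariates named in advance; no covariate is added on the basis of a baseline significance test.' The further covariates should be listed, or stated to be none, before any data by arm are examined.

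The cost is one sentence of analysis wording and agreement on a short list. Parity is already collected before randomisation, no new data are needed, and the total of 140 does not change.

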### Effectiveness Objectives

The primary effectiveness objective of this study is to compare the effectiveness of the Essential Coaching for Every Mother program to standard care on self-efficacy measured immediately after the intervention. The secondary objectives are (1) to compare the effectiveness of the Essential Coaching for Every Mother program to standard care on social support, postpartum anxiety, and postpartum depression immediately after the intervention; (2) to determine whether the effect on any outcomes differs based on parity (multiparous or primiparous); and (3) to compare any long-term impacts of the Essential Coaching for Every Mother program on the above outcomes at 6 months postpartum.

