### Effectiveness Hypotheses

The primary hypothesis is that the Essential Coaching for Every Mother program will result in higher self-efficacy for participants who receive the intervention compared with standard care. The secondary hypotheses are that (1) Essential Coaching for Every Mother will result in higher levels of social support, lower levels of postpartum anxiety, and lower levels of postpartum depression for those who receive the intervention compared with standard care; (2) there will be no difference based on parity on any of the psychosocial outcomes; and (3) changes in psychosocial outcomes will be maintained over time.

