### Sample Size

The sample size was calculated based on the primary outcome of self-efficacy using the findings from our feasibility study [24], which showed a mean difference in self-efficacy scores between baseline and 6-week follow-up of 3.78 (SD 4.5). Therefore, with stratification by parity and a moderate intraclass correlation of ρ=0.2, a sample size of 30 participants per cluster and 60 participants per group (120 total participants) is required to be powered for analysis at the level of parity. In the feasibility study, there was an incompletion rate of 15.5%; thus, the estimated sample size will be increased by 15% to 69 participants per group, rounded up to 70 participants. In total, 140 participants will be enrolled in the study.

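### The parity objective concerns an arm-by-parity interaction, but its test is worded as a four-group comparison and its hypothesis predicts no difference without a margin

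*Protocol article*

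**What the plan says.** Four places in the protocol article bear on this point.

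- **Effectiveness Objectives**, secondary objective 2: "to determine whether the effect on any outcomes differs based on parity (multiparous or primiparous". This is a question about effect modification, on all outcomes.
- **Effectiveness Hypotheses**, secondary hypothesis 2: "there will be no difference based on parity on any of the psychosocial outcomes". No margin is given for what would count as no difference.
- **Data Analysis**, second secondary objective: a 2-way ANCOVA is planned to "measure whether the mean difference of self-efficacy scores differs between the 4 groups (multiparous/primiparous and intervention/control", that is, the cells formed by parity and arm, "with adjustments for any significant covariates on self-efficacy, social support, postpartum anxiety, and postpartum depression". The two preceding analyses in that section are instead specified "with adjustments for the pretest scores and any significant baseline characteristics". The only decision criterion is that a P "value of 0.05 will be considered significant for all outcomes".
- **Sample Size**: 30 participants per cluster and 60 per group, 120 in total, "is required to be powered for analysis at the level of parity". The inputs are a mean change of 3.78 (SD 4.5) from the feasibility study and an intraclass correlation of 0.2.

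**The concern.** Whether an effect differs by parity is a single contrast: the arm difference in primiparous women minus the arm difference in multiparous women. Whether four cell means differ is another question. They also differ when only the arm matters, or when only parity matters. If the sentence is carried out as worded, a program that helps both groups equally would be reported as a parity difference.

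The hypothesis creates the opposite risk. It expects a null result, and the plan offers only a 0.05 threshold to judge it. A non-significant interaction could then be presented as evidence that first-time and experienced mothers benefit equally, although the design leaves wide uncertainty about that. Parity is the stratification factor and the sample size refers to it, so readers will look for this result.

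**Working it through.** **Inputs.** Effect 3.78 and SD 4.5 (Sample Size; a before-after change in the feasibility study, used here as a stand-in for the between-arm effect and the within-cell SD). Cell size n = 30, reading each cluster as one parity-by-arm cell. Alpha 0.05 (Data Analysis), taken as two-sided because sidedness is not stated. Power is not stated either.

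**1. The plan's 30 per cell.** For two arms within one parity group, n = 2 × [4.5 × (1.960 + 1.282) / 3.78]² = 29.8, so 30 per arm at 90% power. This matches the plan's figure only if 90% power was intended and the intraclass correlation is ignored. Using the t distribution, SE = 4.5 × √(2/30) = 1.16, and power at 3.78 is 89%. The 30 per cell therefore fits a comparison within a parity group.

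**2. Four-group reading.** A 3-df F test on four cells of 30 has 116 residual df.
- Same 3.78-point effect in both parity groups, no parity difference, zero interaction: the cell means are 0, 3.78, 0, 3.78. Noncentrality = 30 × 4 × 1.89² / 4.5² = 21.2, and the test rejects 97.8% of the time.
- No program effect, parity groups 2 points apart (an assumed figure), zero interaction: noncentrality = 30 × 4 × 1² / 4.5² = 5.9, and the test rejects 49.8% of the time.

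A significant four-group test therefore says nothing specific about effect modification.

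**3. Interaction reading.** SE = 4.5 × √(4/30) = 1.64.
- 95% CI half-width = 1.981 × 1.643 = 3.25 points.
- Detectable at 80% power: 2.802 × 1.643 = 4.6 points, more than the whole assumed effect.
- Power for an interaction of 3.78 (full effect in one parity group, none in the other): 63%, so it is missed 37% of the time.
- Power for 1.89 (half of that): 21%, so it is missed 79% of the time.
- Cell size for 80% power at 3.78: 4 × (4.5 × 2.802 / 3.78)² = 44.5, so 45 per cell against the planned 30.

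**4. Effect of pretest adjustment.** Taking 4.5 as the SD of the follow-up score, the residual SD is 4.5 × √(1 − r²). For an assumed pre-post correlation r of 0.3, 0.5 or 0.7, the half-width is 3.10, 2.82 or 2.32. If 4.5 is instead a change-score SD, the residual SD is 4.5 × √((1 + r)/2), and the half-width is 3.25 × 0.81, 0.87 or 0.92, that is, about 2.6, 2.8 or 3.0. Adjustment helps, but the interval stays wide relative to 3.78.

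**5. Could the design show no difference?** In an equivalence test (two one-sided 5% tests, true interaction zero, SE 1.64), power is about 49% at an assumed margin of 3.78 and zero at 1.89.

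**The case against.** The strongest reply is that the plan names a 2-way ANCOVA. With arm and parity as crossed factors, that model ordinarily includes a 1-df interaction, whose test keeps its 5% level whatever the main effects are. The bracket lists two crossed factors, the wording can be read as a difference of differences, and the objective itself is stated correctly. This stands: a reader might infer that the plan cannot answer the parity question, and the document does not support that. The rejection rates in step 2 apply only to the literal four-group reading. What remains is that the sentence describes a different contrast and never names the interaction as the test.

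Three further inferences go beyond the text.
- **That pretest adjustment is dropped.** It is not named here, but the significant covariates could include it, and the mean difference could be a change score. It is unspecified and inconsistent with the two preceding analyses. Under randomization, leaving it out would cost precision and would not invalidate the test.
- **That only self-efficacy is tested.** All four outcomes appear in the sentence, though in the covariate clause, and the objective covers them all.
- **That the trial will treat P above 0.05 as proof of equal effect.** Nowhere does the article say so; it states an expectation without a rule for judging it.

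It is also fair that low power for an interaction is common in a secondary objective and no error in itself, and that an article may leave model terms to an analysis plan that is not shown. But a contrast that is described wrongly and a null prediction without a margin are statements made in this article.

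**Conclusion.** The point holds as a mismatch between objective, test wording and hypothesis. The named model is adequate if the interaction is tested; the four-group description is not, and would signal a difference about 98% of the time under an equal 3.78-point effect. Hypothesis 2 cannot be supported by non-significance: the interaction is estimated to within about ±3.25 points, or roughly ±2.3 to ±3.1 with pretest adjustment at assumed correlations of 0.3 to 0.7, against an assumed whole effect of 3.78. The power statement in Sample Size fits comparisons within a parity group (about 89%, ignoring the intraclass correlation) and should not be read as covering a difference between parity groups (63% at the same size).

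These figures assume that the feasibility SD of 4.5 applies within cells, that tests are two-sided, and that 30 women per cell complete follow-up.

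**What to change.** - **Data Analysis:** for each of the four outcomes, fit arm, parity, arm-by-parity and that outcome's baseline score. Name the interaction as the test for secondary objective 2. Report its estimate with a 95% CI, and the arm effect within each parity group.
- **Effectiveness Hypotheses:** reword hypothesis 2 as estimation of the difference in effect, and state that a non-significant interaction will not be read as equal effect.
- **Sample Size:** state that the power refers to comparisons within each parity group.

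The cost is wording only: the baseline scores are already collected, and no extra participants are needed. The trade-off is that the trial gives up a claim of equal effect across parity.

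### The parity (objective 2) model does not guarantee adjustment for the pretest score, which can cost precision in the least precise comparison

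*Protocol article*

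**What the plan says.** The Data Analysis section of the protocol article sets out the models one after another, in different words.

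- **Primary outcome:** an ANCOVA of "whether total self-efficacy scores differ between the 2 groups, with adjustments for the pretest scores and any significant baseline characteristics".
- **First secondary objective:** an ANCOVA of scores "on social support, postpartum anxiety, and postpartum depression, with adjustments for the pretest scores and any significant baseline characteristics".
- **Second secondary objective (parity):** "a 2-way ANCOVA will be used to measure whether the mean difference of self-efficacy scores differs between the 4 groups" formed by parity and arm, "with adjustments for any significant covariates on self-efficacy, social support, postpartum anxiety, and postpartum depression".

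The pretest score is named in the first two and not in the third. The mean difference is not defined there. The Sample Size section uses the same term for change from baseline to 6 weeks: "a mean difference in self-efficacy scores between baseline and 6-week follow-up of 3.78 (SD 4.5"). The Effectiveness Objectives section frames objective 2 as effect modification by parity for all outcomes, whereas the analysis sentence names only self-efficacy as the response. Table 1 shows that all four scales are collected at baseline.

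**The concern.** Two models fix the pretest as a covariate in advance, and the third leaves it to a significance rule. The only such rule in the Data Analysis section is a chi-square or Mann-Whitney test for differences in baseline characteristics. If that rule governs the parity model, and baseline is compared between the arms, a pretest that is well balanced is left out however strongly it predicts the 6-week score. With randomised arms and a true baseline, it would qualify only about 5% of the time.

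What is at stake is precision in a secondary objective. The arm-by-parity interaction is the least precise of the planned comparisons. The Effectiveness Hypotheses section also predicts no difference by parity, so a wide interval could be misread as support for that prediction.

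**Working it through.** **Inputs.** From Sample Size: difference 3.78, SD 4.5, 30 per parity-by-arm cell, 60 per arm. From Data Analysis: significance level 0.05, taken as two-sided. Not in the documents: power, and the correlation r between baseline and 6-week scores. I take r = 0.3, 0.5 and 0.7, and add 0.88, the test-retest reliability given under Effectiveness Outcomes for the self-efficacy scale, as an upper guide only.

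**1. The plan's own figure.** The Sample Size section gives 30 per cell, and so 120 in all, as the number needed for an analysis by parity. For two means, n per arm = 2(1.960 + 1.282)² × (4.5/3.78)² = 2 × 10.51 × 1.417 = 29.8, so 30 at 90% power. At 80% power it would be 23. The stated 30 is therefore reproduced as a comparison of arms within one parity stratum, without using the quoted intraclass correlation of 0.2. It is not reproduced as a test of interaction.

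**2. Precision of the interaction.** With a common residual SD of 4.5:

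- overall arm effect: SE = 4.5 × √(2/60) = 0.82
- arm-by-parity interaction: SE = 4.5 × √(4/30) = 1.64, twice as large.

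**3. Cost of leaving out the pretest.** With equal variance s² at both times:

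- change score: 2s²(1−r)
- 6-week score alone: s²
- pretest-adjusted ANCOVA: s²(1−r²).

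The variance ratios against ANCOVA are therefore 2/(1+r) for unadjusted change and 1/(1−r²) for the unadjusted 6-week score. The SE ratio is the square root of the first.

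| r (assumed) | Change: variance ratio | Change: SE ratio | 6-week score: variance ratio |
|---|---|---|---|
| 0.3 | 1.54 | 1.24 | 1.10 |
| 0.5 | 1.33 | 1.15 | 1.33 |
| 0.7 | 1.18 | 1.08 | 1.96 |
| 0.88 | 1.06 | 1.03 | 4.43 |

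**4. In terms of power.** Read 4.5 as the SD of change, which fits its use in Sample Size. The ANCOVA residual SD is then 4.5 × √((1+r)/2), and the interaction SE is that value × √(4/30). Power is Φ(3.78/SE − 1.96) for an interaction of 3.78. That is a benchmark only, since it is as large as the whole assumed effect.

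- Change without pretest: SE 1.64, power 63%.
- With pretest: SE 1.32, 1.42, 1.51 and 1.59, and power 81%, 76%, 70% and 66%, at r = 0.3, 0.5, 0.7 and 0.88.

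**5. Does the response matter once the pretest is in?** No. Change is the 6-week score minus the pretest. Subtracting a covariate from the response lowers that covariate's own coefficient by 1 and leaves the arm and interaction estimates and their standard errors unchanged.

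**The case against.** The strongest reply is that the article never says the pretest is left out. The covariates in the parity sentence could include baseline scores on the four scales, and a full protocol or SAP may list them. If a covariate qualifies by its association with the outcome, the pretest would probably enter and most of the loss would disappear. The response is also open: mean difference could denote a between-arm difference. All of this stands, and it limits the point to a missing guarantee. It does not remove the point, because the article itself fixes a covariate rule for this model that is weaker than the one in the two models before it.

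The cost may also be small. On the change-score reading at r = 0.88 it is 6% in variance, about 3% in SE. That stands too.

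A reader might infer three further things that the documents do not support:

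- **A ceiling distortion.** If parity groups start at different levels on a scale capped at 45, raw change might seem to mislead. Randomisation is stratified by parity, so baseline differences between parity groups are balanced across arms in expectation and largely cancel in the arm-by-parity contrast. A linear pretest term would not cure a ceiling in any case.
- **Conflicting results.** The parity model and the primary ANCOVA need not agree on the arm effect, but nothing shows that they will conflict. Under randomisation both target the same quantity.
- **A wrong response.** Change is not an error in itself, as step 5 of the working shows.

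**Conclusion.** The point holds in limited form. Pretest adjustment is fixed for the primary and first secondary models and only conditional for the parity model. The stronger statement, that the parity model omits the pretest, goes beyond the text.

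Where the pretest does not enter, the interaction variance is 6% to 54% larger than it need be on the change-score reading (r from 0.88 down to 0.3). It is 10% to 96% larger on the unadjusted 6-week-score reading (r from 0.3 to 0.7). These sizes rest on assumed r, equal variances at the two times and no ceiling. No bias or invalid test follows, and the primary result is untouched. It should be corrected because the gain in precision is almost free and the comparison has little to spare.

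**What to change.** Rewrite the objective 2 sentence. For each of the four scales, fit a model with the 6-week score as response, and arm, parity, arm-by-parity and the same scale's pretest score as terms. Include the pretest whatever its P value, and name the arm-by-parity term as the test of the objective. Stating the response as the 6-week score is for clarity only.

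The cost is one sentence and one degree of freedom per model; no new data are needed. One limitation should be acknowledged: under Screening and Baseline, participants learn their allocation before they are asked to complete the baseline survey, so the pretest may not be a clean baseline. The primary ANCOVA and any change score share that limitation, so it is no reason to treat the parity model differently from the primary.
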